### Participant Incentives

Upon completing the 2-hour laboratory-based session, participating families will receive one US $30 Amazon gift card, for a rate of US $15 per hour, the standard rate approved by the University IRB and consistent with minimum wage in New York State. When each participating adolescent and parent complete the 3-month follow-up questionnaire, the family will receive a US $10 Amazon gift card, again based on a US $15 per hour rate. Similarly, when the adolescent and parent both complete the 9-month follow-up questionnaire, the family will receive a final US $10 Amazon gift card. Thus, total compensation for participating in this study is US $50.

### Follow-Up Assessments

To enable evaluation of the interventions’ effects on depressive symptoms and secondary study outcomes over time, each adolescent and parent will be invited to complete Qualtrics-based questionnaire batteries, including the same questionnaires as those they completed at their initial laboratory session. Links to Qualtrics surveys will be sent to families at 3- and 9-month follow-up points. Surveys may be conducted via phone at the family’s request. Families who do not complete the follow-up questionnaires within 3 days of receipt will receive up to 3 reminder messages from the research team to encourage survey completion.

Notably, logistical constraints necessitated our limiting the number of follow-up assessments in this study to 2 per family (at 3- and 9-month postintervention), and analyses were planned accordingly (see below for a more thorough description). We elected a final follow-up assessment at the 9-month mark to maintain consistency with previous trials of GMI [13,14].

After the study is complete, an aggregate results summary will be emailed to families. Condition assignment will be revealed at this time, and all youths will receive access to both Web-based interventions. Youths who did not receive the VR program will be invited to complete the intervention at Stony Brook University.

### Questionnaires

Table 2 displays a timeline of all study procedures, including points at which each questionnaire will be administered to parents and/or youths. All questionnaires are detailed below.

#### Family and Treatment History Questionnaire

Parents will report demographic, family, and other background information (eg, age, sex, race, childhood adversity exposure, and mental health treatment history). Parents will also complete the 4-item Pubertal Development Scale [30] with regard to their adolescent, given the well-documented effects of puberty on depression onset.

#### Children’s Depression Inventory-2

Adolescent depressive symptom severity will be assessed using the CDI-2 [31] child form (youth-report) and parent forms (parent-report). The CDI-2 is a reliable, valid measure of youth depression severity, normed for youth age and sex and yielding raw and *T* scores. Changes in youth-report CDI-2 scores from baseline to each of the follow-up assessments (3-month and 9-month) will serve as the primary index of intervention effects. Changes in parent-report CDI-2 scores from baseline to each of the follow-up assessments (3-month and 9-month) will serve as a secondary index of intervention effects. The CDI-2 will not be administered to youths or to parents immediately postintervention, as we do not expect depressive symptom change to occur within the span of 1 study session. Changes in scores on other assessments will serve as secondary outcomes.

#### Screen for Child Anxiety and Related Disorders

Given high comorbidity between depression and anxiety [32], anxiety symptoms will be assessed at baseline and all follow-ups (except postintervention) using the Screen for Child Anxiety and Related Disorders-Child and -Parent versions (SCARED-C/SCARED-P): a 41-item self-report measure [33,34]. Youths and parents, respectively, rate (0 to 2) the degree to which statements describing anxiety symptoms are true about them or their adolescent. Higher summed SCARED-C and SCARED-P total scores indicate greater adolescent anxiety severity.

#### Primary Control Scale for Children

The primary control scale for children (PCSC) [35] is a 24-item scale measuring youths’ perceived ability to influence or alter objective events or conditions through personal effort. Youth rate agreement with statements about their ability to exert primary control (eg, “I can do well on tests if I study hard” and “I can get other kids to like me if I try”). The PCSC has shown acceptable internal consistency, 6-month test-retest reliability, and inverse relations to adolescent depression severity.

#### Secondary Control Scale for Children

The secondary control scale for children (SCSC) [19] is a 20-item scale measuring youths’ perceived ability to shape the personal impact of objective conditions on oneself by adjusting oneself to fit those conditions. Youth rate agreement with items reflecting various kinds of secondary control such as adjusting cognition (“When something bad happens, I can find a way to think about it that makes me feel better”). The SCSC has shown acceptable reliability and validity in a large youth sample.

#### Implicit Personality Theory Questionnaire

The Implicit Personality Theory Questionnaire [36] asks the youth to rate the extent of their agreement with 3 statements linked to the malleability of personality, using a 1 to 7 Likert scale (eg, “Your personality is something about you that you can't change very much”). Higher mean scores on these 3 items indicate a stronger fixed personality mindset, a lower score indicates a stronger growth personality mindset. Both youths and parents will report their mindsets of personality in this study.

#### University of California Los Angeles Loneliness Scale

The UCLA Loneliness Scale [37] is a widely used self-report scale of loneliness in adolescents. The 20-item version will be used in this study. Adolescents rate how often they experience loneliness in various contexts (eg, “How often do you feel part of a group of friends?” and “How often do you feel there is no one you can turn to?”). Higher scores indicate higher levels of loneliness.

#### Beck Hopelessness Scale—Short Version

The Beck Hopelessness Scale (BHS)-4 [38] is a shortened version of the 20-item BHS [39] designed for brief psychological screening purposes. The 4 items on this measure are “My future seems dark to me”; “Things just won’t work out the way I want them to”; “There is no use in really trying to get something I want because I probably won’t get it”; and “I feel that the future is hopeless and that things cannot improve.” On each item, participants rate their agreement from 0 to 3, resulting in a maximum of 12 points in total (higher scores indicate higher levels of hopelessness). The short version of the BHS has high internal consistency (alpha=.85) and correlates highly with measures of depressive symptoms, as well as the full-length BHS, in large studies of clinical and community samples [40].

**Table 2 table2:** Schedule of enrollment, interventions, and assessments.

Schedule			Study period					
			Enrollment	Allocation (baseline)	Post-allocation			Close-out (9 months)
					Intervention administration	Immediate post-intervention	3 months	
**Enrollment**								
	Eligibility screen		X	—^a^	—	—	—	—
	Informed consent/assent		X	—	—	—	—	—
	Allocation		—	X	—	—	—	—
**Interventions^b^**								
	VR GMI^c^		—	—	X	—	—	—
	Web-based GMI^d^		—	X	—	—	—
	Web-based ST^e^		—	X	—	—	—
**Assessments**								
	**Youth self-report**						
		Children's Depression Inventory 2-Youth	—	X	—	—	X	X
		Screen for anxiety related disorders-Youth	—	X	—	—	X	X
		Primary control scale for children	—	X	—	X	X	X
		Secondary control scale for children	—	X	—	X	X	X
		Beck Hopelessness Scale-Short form	—	X	—	X	X	X
		UCLA^f^ Loneliness Scale-Version 3	—	X	—	X	X	X
		Implicit personality theories questionnaire	—	X	—	X	X	X
		Attitudes toward therapy scale	—	X	—	X	X	X
		Program feedback scale	—	—	—	X	—	—
	**Parent report**							
		Family demographics, youth treatment history	—	X	—	—	—	—
		Children's depression inventory 2-parent	X	X	—	—	X	X
		Screen for anxiety related disorders–parent	—	X	—	—	X	X
		Implicit personality theories questionnaire	—	X	—	—	X	X
		Attitudes toward therapy scale	—	X	—	—	X	X
		Brief symptom inventory-18	—	X	—	—	X	X

^a^Not applicable.

^b^Each ~30 minutes in length; randomized to receive 1 of 3.

^c^VR GMI: virtual-reality growth mindset intervention.

^d^GMI: growth mindset intervention.

^e^ST: supportive therapy.

^f^UCLA: University of California Los Angeles.

#### Brief Symptom Inventory 18

The Brief Symptom Inventory (BSI)-18 [41] is a valid, reliable screening tool for adult (here, parental) psychological distress. Adult respondents rate endorsement of 18 physical and emotional complaints on a 0 to 4 Likert scale. The BSI-18 includes 3 subscales for somatic, anxiety, and depressive symptoms. The total sum score yields an additional total distress score.

#### Attitudes Toward Therapy

Attitudes toward psychotherapy [42] will be assessed using a single item for youth and parents: “Lots of kids deal with difficult emotions at one time or another. On a scale from 1 (not at all helpful) to 10 (extremely helpful), how helpful do you think therapy or counseling would be for you (your child) in coping with these kinds of problems?”

#### Program Feedback Scale (Designed for This Study)

To assess the acceptability of each intervention program, youths will be asked to complete questions regarding their experience with the intervention to which they were assigned. Questions inquire about how much they enjoyed the program; whether they understood the program; whether they would recommend the program to a friend; and whether they found the program easy to use. The Program Feedback Scale was developed specifically for this study; several items from the Scale were drawn from previous research [13,14] but others are new to this study and have not been used previously. All items are included in Textbox 1.

Program Feedback Scale items. Items rated on a 0 (really disagree) to 4 (really agree) scale unless otherwise specified.I enjoyed the programI understood the programThis program was easy to useI tried my hardest during the programI think the program would be helpful to other kids my ageI would recommend this program to a friend going through a hard timeI agree with the program’s messageWhat did you like about the program? Please share as many true thoughts and feelings as you would like (*free response*)What would you change about the program? Please share as many true thoughts and feelings as you would like (*free response*)

### Timeline for Data Collection and Results Reporting

Data collection began in March 2019 and is projected to be complete by December 2021. Thus, we intend to report results by Spring of 2022. Upon completion of data collection and publication of results, deidentified participant-level data will be made publicly accessible.

## Results

### Aim 1: Attempt to Replicate Past Research

We will use mixed-effects linear models to test the hypothesis that interventions teaching GM (either VR or Web-based) predict reductions in adolescent depressive symptom severity (primary study outcome), per both adolescent and parent reports, relative to Web-based ST. Our study design, including 3 assessment points is structured to allow for detection of linear intervention effects. We will run additional mixed-effects linear models to assess whether interventions teaching GM predict larger improvements in secondary study outcomes (perceived primary and secondary control, hopelessness, loneliness, attitudes toward psychotherapy, and parent psychopathology) versus Web-based ST. Intervention condition will be a binary predictor variable in these models, with the VR GMI and Web-based GMI groups collapsed into a single *GM* intervention group. Potential covariates will include family income, age, sex, and time (baseline, postintervention where applicable, and 3-month and 9-month follow-up); each possible covariate will be included in analyses if it shows a significant association with a model outcome at baseline or any follow-up point (such associations are unlikely to occur, given randomization procedures, but remain possible). Models will include a random intercept and slope, an autoregressive error structure, and use full information maximum likelihood (FIML) estimation to address missing data. We will create 2 orthogonal planned contrasts for testing intervention effects. One planned contrast will examine whether the 2 active GM conditions differ from the ST control condition, whereas the other planned contrast will examine whether the VR-based intervention outperforms the Web-based intervention. A significant (*P*<.05) interaction between the first contrast and time would indicate that interventions teaching GM predicted significantly different 9-month change in an outcome relative to the control ST condition. We will also replicate these analyses for the most central symptoms of adolescent depression identified in previous analyses (*sadness*, *self-hatred*, and *loneliness*) and use Holm-Bonferroni corrections for multiple comparisons.

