Notably, a recent systematic review of studies evaluating VR applications for mental health identified only 2 studies that have tested immersive VR mental health treatment approaches; both were uncontrolled feasibility trials targeting adults [19]. Thus, to our knowledge, this study will be the first randomized trial evaluating a brief VR intervention for adolescent depressive symptoms.

This research has 4 specific aims. Our first aim is to replicate past research suggesting that GM SSIs can significantly reduce depressive symptoms in at-risk adolescents. We hypothesize that adolescents aged 12 to 16 years who participate in a GMI (Web-based *or* VR–based) will show larger reductions in depression symptoms from baseline through the 9-month follow-up assessment compared with adolescents who receive an active, Web-based control program.

Our second aim is to evaluate new, single-session, VR GMI including a comparative efficacy study. Our second aim is to also evaluate whether the new VR–based GM SSI (the VR Personality Project) can reduce depressive symptoms in adolescents, both relative to an active control program and to the previously tested Web-based GM SSI [13,14]. We hypothesize that adolescents who participate in the VR–based GM SSI will show larger reductions in depressive symptoms from baseline through the 9-month follow-up assessment compared with adolescents who receive the Web-based GMI *and* compared with adolescents who receive the active Web-based control program.

Our third aim is to test whether shifts in perceived control mediate intervention effects on adolescent depressive symptoms. The VR Personality Project was designed to target and increase adolescents’ perceived control by offering a more immersive, active, and user-directed intervention experience than the Web-based GM SSI can provide. Thus, the third goal of this study is to examine whether the VR Personality Project does, in fact, reduce adolescent depressive symptoms by eliciting proximal increases in perceived control. We hypothesize that the VR Personality Project will lead to larger increases in immediate postintervention perceived control than the Web-based intervention from pre- to postintervention and that these increases will mediate subsequent reductions in adolescent depression across the follow up period.

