### Aim 2: Evaluate New, Single-Session, Virtual Reality Growth Mindset Intervention

As for Aim 1, we will use mixed-effects linear models to test the hypothesis that VR-GMI predicts greater reductions in adolescent and parent-reported depressive symptom severity (primary study outcomes), as well as perceived primary and secondary control, hopelessness, loneliness, attitudes toward psychotherapy, and parent psychopathology (secondary outcomes), relative to (1) the Web-based GM program, (2) the control program, and (3) either program, when combined into a single, *non-VR intervention* group. Models will be structured as described in Aim 1. A significant (*P*<.05) interaction between the second orthogonal contrast mentioned in Aim 1 and time would indicate that interventions teaching GM predicted significantly different 9-month change in an outcome relative to the control ST condition. We will also replicate these analyses for the most central symptoms of adolescent depression identified in previous analyses (*sadness*, *self-hatred*, and *loneliness* [43]) and use Holm-Bonferroni corrections for multiple comparisons.

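### A single linear time slope cannot estimate the two changes named as the primary index, and the 3-month change is left untested

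*Protocol article*

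**What the plan says.** The Methods section on the Children's Depression Inventory-2 defines the primary index: "Changes in youth-report CDI-2 scores from baseline to each of the follow-up assessments (3-month and 9-month) will serve as the primary index of intervention effects". The same section says that "The CDI-2 will not be administered to youths or to parents immediately postintervention", so the primary outcome has three visits: baseline, 3 months and 9 months.

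The Aim 1 section then sets the analysis. It states "Our study design, including 3 assessment points is structured to allow for detection of linear intervention effects", and continues: "Models will include a random intercept and slope, an autoregressive error structure". The test is a single interaction at the 5% level: a significant "interaction between the first contrast and time would indicate that interventions teaching GM predicted significantly different 9-month change in an outcome". For Aim 2 the article says "Models will be structured as described in Aim 1", so the VR comparisons inherit the same test.

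The Objectives section words the Aim 1 hypothesis over the whole period: adolescents given a growth mindset programme "will show larger reductions in depression symptoms from baseline through the 9-month follow-up assessment compared with adolescents who receive an active, Web-based control program".

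Time is listed in Aim 1 by visit label only. No numeric scoring is given.

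**The concern.** The primary index contains two changes and the primary test estimates one number. A random slope needs a numeric time variable, and the stated purpose is to detect linear effects, so the interaction is a difference between groups in rate of change. That rate equals the 9-month change, as the article reads it, only under conditions the article does not set out. The 3-month change is never tested separately.

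The shape of the effect matters because the intervention is one session of about 30 minutes with nothing delivered afterwards. A benefit that appears by 3 months and then holds or fades is at least as plausible as one that grows steadily for 9 months. Under such a course the slope may understate the 9-month effect, and the trial may lose power it can hardly spare: the sample size section says that logistics already restrict it to medium effects.

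**Working it through.** **The plan's own figure.** The sample sizes of 969, 159 and 66 reproduce for a three-group omnibus F test at alpha 0.05, using f = 0.10, 0.25 and 0.40 (half of d = 0.2, 0.5 and 0.8). Power is 0.801, 0.805 and 0.818. That calculation concerns one-way group means and says nothing about a slope, so the plan gives no figure for the test at issue.

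**Inputs from the article.** Visits at 0, 3 and 9 months; 53 per arm; Aim 1 contrast 106 against 53; d = 0.5. **Assumed:** complete data, equal correlation r between visits, separate baseline terms by group for the slope. The article gives no correlations or dropout rate.

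**Slope weights, time in months.** The mean time is 4, the deviations are -4, -1, 5, and their sum of squares is 16 + 1 + 25 = 42. The slope is (-4·Y0 - 1·Y3 + 5·Y9)/42. Multiplied by 9, the implied 9-month change is

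-0.857·Y0 - 0.214·Y3 + 1.071·Y9.

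**Slope weights, visits scored 0, 1, 2.** The deviations are -1, 0, 1 with sum of squares 2. Multiplied by 2, the implied change is -Y0 + 0·Y3 + Y9.

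**What each returns** (group difference in benefit, zero at baseline):

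| Difference at 3 and 9 months | True 9-month effect | Months scoring | 0/1/2 scoring |
|---|---|---|---|
| 1/3, 1 (proportional to time) | 1 | 1.00 | 1 |
| 1, 1 (sustained) | 1 | 0.86 | 1 |
| 1, 0.5 (half faded) | 0.5 | 0.32 | 0.5 |
| 1, 0.2 | 0.2 | 0.00 | 0.2 |
| 1, 0 (fully faded) | 0 | -0.21 | 0 |

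For example, half faded: -0.214 × 1 + 1.071 × 0.5 = 0.32. No row under either scoring returns the 3-month change.

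**Sensitivity of the 3-month weight (-0.214).**
- Autoregressive errors by visit index, rho 0.3 to 0.9: -0.30 to -0.55. By months: -0.10 to -0.002.
- 20% missing at 9 months: -0.11 to -0.14. 40% missing: -0.02 to +0.04.
- Log or square-root months: +0.13 or +0.10.
- Baseline means forced equal, r from 0.3 to 0.7: +0.11 to -0.09.

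**Power, sustained d = 0.5, r = 0.5.** Power = Φ(effect/SE - 1.96), with SE² = k(1/106 + 1/53) = 0.0283k.
- Month-scored slope: k = (1 - r)(0.735 + 0.046 + 1.148) = 0.964; SE = 0.165; effect 0.857 × 0.5 = 0.429; power Φ(0.63) = 0.74.
- 9-month change: k = 2(1 - r) = 1; SE = 0.168; power Φ(1.01) = 0.84.
- Baseline-adjusted 9-month contrast: k = 1 - r² = 0.75; SE = 0.146; power Φ(1.47) = 0.93.

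For a pairwise comparison (53 against 53) the same formulas give 0.61, 0.73 and 0.84. If the effect instead grows linearly to 0.5, the Aim 1 slope has power Φ(0.5/0.165 - 1.96) = 0.86, against 0.84 for the unadjusted 9-month change.

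**The case against.** The best defence is that the linear model is a disclosed choice with reasons. Aim 1 is a replication, the Introduction reports steeper 9-month declines in the earlier trial, and the Follow-Up Assessments section says that logistics limited follow-up to two assessments and that the analyses take this into account. The Objectives hypothesis runs from baseline through 9 months, which a trajectory test addresses. The scoring of time is the kind of detail a journal article leaves to its analysis plan. All of this is fair, and the missing scoring is not held against the article here. But none of it reconciles two named changes with one tested slope. If time were a factor instead, the interaction for three visits would have two degrees of freedom and could not be read as 9-month change alone.

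A reader might infer more than the document supports:
- *That the test counts a 3-month benefit against the intervention or reverses its sign.* This needs month scoring and mostly complete data, and reversal also needs more than about 80% of the 3-month effect to be lost by 9 months. Visit scoring, heavy dropout or equal baseline means can remove the negative weight.
- *That immediate effects on control, hopelessness, loneliness and attitudes are halved.* With months 0, 0, 3, 9 the weights are -0.5, -0.5, 0, 1, so an immediate sustained effect of 1 is estimated as 0.5. With visits scored 0 to 3 the weights are -0.9, -0.3, 0.3, 0.9 and the estimate is 0.9. These are secondary outcomes, and the point depends on the scoring.
- *That the power loss is about 20 points.* The pairwise gap from 0.61 to 0.84 mixes the slope loss with the gain from baseline adjustment. Against the unadjusted 9-month change, the slope loses about 10 points in the Aim 1 contrast and 12 pairwise.

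**Conclusion.** The mismatch stands, whatever the scoring of time. The article names change to each of two follow-ups as its primary index, and its primary analysis estimates a single slope. The 3-month change goes untested in Aims 1 and 2.

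Whether the slope also misstates the 9-month change is conditional. With month scoring and mostly complete data it is right only for a difference that grows in proportion to time; it gives 0.86 of a sustained effect and 0.32 where the truth is 0.5. With 0/1/2 scoring it is right for any course. The power figures rest on an assumed correlation of 0.5, complete data and a sustained effect. At r = 0.7 the pairwise slope and 9-month change have power 0.83 and 0.91, so the ordering holds but the gap narrows.

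**What to change.** Replace linear time with categorical visit and an unstructured covariance matrix. Adjust for baseline, or constrain baseline means to be equal across arms. Estimate the group contrasts at 3 and 9 months from this model. Name the 9-month contrast in youth-report CDI-2 as primary and the 3-month contrast as key secondary, and amend the definition of the primary index to match. Apply the same structure in Aim 2 and, with four visits, to the outcomes also measured straight after the session. Keep the linear-slope model as a sensitivity analysis and state how time is scored in it.

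This needs no new data and no change to visits, only revised analysis wording and a different specification in mixed-model software, settled before unblinded analysis. The cost is a slight loss of efficiency if the true course is exactly linear: 0.84 against 0.86 in the example above, both without baseline adjustment.

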### Detailed Study Procedures

#### Recruitment and Screening

Youth participants will be recruited from community groups, after-school and extracurricular programs, parent organizations, private psychiatric and pediatric primary care clinics, and religious organizations in the Stony Brook area. Eligibility for participation will be ascertained through a parent phone screen conducted by a trained member of the research team. Parents will be informed at the end of the phone screen whether or not their adolescent qualifies for study participation. Youths must be living with at least 1 parent or legal guardian and both must speak English well enough to complete study interventions. Additional inclusion criteria will include the following: (1) the youth is aged 12 to 16 years (inclusive) with 1 parent willing to participate (2) the youth reports elevated depressive symptoms (>80 percentile for age and sex, reflecting subclinical or higher symptom elevations) based on the parent-report version of the Children’s Depression Inventory-2 (CDI-2). Exclusion criteria will include intellectual disability (based on parent report) and hospitalization of the adolescent within the past 2 months for suicide attempt or self-harm, as the interventions being evaluated in this study are not designed for youth with acute medical or psychiatric need. Concurrent treatment will not preclude eligibility. Youths prone to seizures will also be eligible to participate; risks of participating will be discussed with prospective participants and families before study participation. This study will focus on youth aged 12 to 16 years because depression increases markedly in adolescence, and youth in this age range have responded well to GMI [13,14].

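### Covariates, and on the wording even time, enter the models only if significantly associated with an outcome; the randomisation rationale is wrong, though the effect on the main test should be small

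*Protocol article*

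**What the plan says.** The rule is in the protocol article, Results, Aim 1: Attempt to Replicate Past Research. The candidates are given as "Potential covariates will include family income, age, sex, and time". The entry condition is that "each possible covariate will be included in analyses if it shows a significant association with a model outcome at baseline or any follow-up point", followed by the reason: "such associations are unlikely to occur, given randomization procedures, but remain possible". No significance level is given for this screen. It is also unclear whether association with one outcome admits a covariate to the models for all outcomes.

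The same section specifies the model: "Models will include a random intercept and slope, an autoregressive error structure", with full information maximum likelihood (FIML) for missing data. It builds two orthogonal planned contrasts, and the test is that a significant "interaction between the first contrast and time would indicate that interventions teaching GM predicted significantly different 9-month change in an outcome" relative to the control. Aim 2 says its models follow the Aim 1 structure, so the covariate rule applies there too.

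**The concern.** There are three faults in what is written.

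- **The rationale confuses two associations.** Randomisation protects against association between a covariate and the arm. The rule concerns association between a covariate and the outcome, on which allocation has no bearing.
- **The adjustment set is data-dependent.** Screening against follow-up outcomes means the model is settled only after post-randomisation data are seen. The set can differ between youth-report and parent-report CDI-2 and between secondary outcomes. FIML assumes data are missing at random given the variables in the model, so that assumption also changes with the screen.
- **Time is in the optional list.** A contrast-by-time interaction and a random slope both presuppose time in the model. The screen cannot be applied to time visit by visit, because time is constant within a visit.

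At stake are a primary model that is not fully fixed in advance, room for analyst choice, and an internal contradiction that a programmer would have to resolve.

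**Working it through.** **Inputs.** From the protocol article: N = 159, 53 per arm (power analysis section); three CDI-2 assessments, at baseline, 3 and 9 months (CDI-2 section and Table 2); the rule and model above (Aim 1). Assumed, because the article gives no values: a two-sided .05 level for the screen, covariate-outcome correlations, between-visit correlations, variance components and missingness.

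**1. The plan's own figure.** For an omnibus one-way ANOVA with three arms, alpha .05 and power .80, a noncentral F calculation with f = .25 gives N = 159 (power .805), as stated. This figure is not in dispute and is used only as n below.

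**2. Are covariate-outcome associations unlikely?** By Fisher's z, P(significant at one visit) = Φ(z − 1.96) + Φ(−z − 1.96), where z = atanh(r) × √(159 − 3) = atanh(r) × 12.49. For r = .20, z = 0.2027 × 12.49 = 2.53, and Φ(0.57) is about .72.

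| Assumed r | P(significant at one visit) |
|---|---|
| 0 | .05 |
| .10 | .24 |
| .20 | .72 |
| .25 | .89 |
| .30 | .97 |

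Over any of three visits, r = .20 is selected in 86% to 90% of simulated trials (between-visit correlation .7 to .5). The allocation method appears nowhere in this formula.

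**3. How often does noise enter?** For a covariate with no true association, the bound with three independent visits is 1 − .95³ = .143; simulation with correlated visits gives .11 to .13. For at least one of three such covariates, the bound is 1 − .95⁹ = .370; simulation gives .30 to .33.

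**4. Does the screen disturb the test?**

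- *Final-visit contrast, 106 versus 53, no treatment effect* (6,000 runs per setting, covariate correlations 0, .2 and .3; Monte Carlo error √(.05 × .95/6000), about 0.3 points). Type I error was 5.1–5.2% with no covariates, 4.9–5.2% with all three, and 4.9–5.3% with the screened set.
- *Contrast-by-time with random intercept and slope* (covariance treated as known, no autoregressive term). With complete data the interaction estimate was identical with none, all or screened covariates, and type I error was 5.5% for all three (800 runs, Monte Carlo error about 0.8 points). The reason is structural: age, sex and income are constant over time, and the plan names no covariate-by-time terms, so they adjust the level and not the slope contrast.
- *The same model with an assumed 20% missing at follow-up.* Type I error was 4.6–4.8%, and the estimate moved by at most 0.03 against a standard error of 0.15, that is 0.2 SE. A separate simulation under its own assumptions gave an average movement of about 0.02 SE and a maximum of 0.10 SE.

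**5. What if time were left out?** Let the slope common to all arms be b, with no treatment effect.

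- *0/1 coding (GM = 1, ST = 0).* Without a time term the ST slope is forced to zero, so the interaction coefficient is the whole GM slope: bias = b. Simulation agrees: b = −0.50 gave about −0.50.
- *Orthogonal contrast (1/3, 1/3, −2/3), equal arms.* The contrast sums to zero over participants (53/3 + 53/3 − 2 × 53/3 = 0), so the omitted common slope is orthogonal to the contrast-by-time term: bias = 0. Simulation with the same b gave about 0.00.

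**The case against.** The strongest reply is that the rule has almost no consequence for the stated test. Step 4 bears this out, and it stands. Two stronger conclusions that a reader might draw are therefore not supported.

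- *That P values after the screen are not nominal.* Selection frequencies alone do not show this. The screen ignores arm, the covariates are measured before randomisation, and the simulated error rates stay near 5%.
- *That the decline common to all arms would be credited to the growth mindset arms.* This needs 0/1 coding, time dropped, and a real decline, all together. Aim 1 does mention a binary condition variable, but the decision rule is stated for the orthogonal contrasts. A substantial decline would tend to pass a significance screen and so keep time in. When time was put through such a screen rather than always omitted, simulated false rejection stayed at or below about 8% even under 0/1 coding. The random slope and interaction also make it likely that time would be kept in practice.

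It is also tempting to say that the protocol itself expects an age association, since Recruitment and Screening says that "depression increases markedly in adolescence". That sentence explains the age range. Entrants are selected above a percentile normed for age and sex, and the CDI-2 is normed likewise, so T scores might show little age or sex association within the sample. But the article does not say whether raw or T scores are analysed, norming does not cover family income or the other outcomes, and norming is not the reason the plan gives.

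Finally, this is not detail left to an analysis plan. The article states a rule and a reason for it, and both can be judged as written.

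**Conclusion.** The point holds as a minor one. The randomisation rationale is wrong as stated, the screen makes the adjustment set depend on post-randomisation outcomes, and making time optional contradicts the model and test in the same section. These three conclusions follow from the text and need no assumed figures.

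The size is limited. Type I error is expected to stay near 5%. The contrast-by-time estimate is unchanged with complete data and moves by a small fraction of its standard error with 20% missing. Those results rest on assumed variances and correlations, covariates entered as main effects only, and simplified models (a single-visit contrast, or a known covariance without the autoregressive term). The absence of bias when time is omitted rests on equal arms and the orthogonal contrasts. What remains is a model not fully specified in advance, possible inconsistency between outcomes and informants, and a missing-data assumption that shifts with the screen.

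**What to change.** In Aim 1, and by reference in Aim 2:

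1. State that time, the contrasts and the contrast-by-time terms are in every model, and take time out of the list of potential covariates.
2. Name the baseline covariate set in advance, for example age, sex and family income, and use it in every model whatever its significance. A fixed unadjusted model would also remove the data-dependence; the essential step is to choose before outcomes are examined.
3. Delete the significance screen and the sentence on randomisation.

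The cost is a wording change and about 3 degrees of freedom with 159 participants. The three covariates are already named in the plan, so no new participants or measures are needed.
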